### Control group

Normal practice will be used in counselling controls, following the clinical practice guidelines of the Catalan Health Institute.

### Measures

During the recruitment visit, sociodemographic and anthropometric variables will be recorded: age, sex, educational level, employment, weight, height and blood pressure. Social class will be categorized according to the British Registrar General’s Social Classification [11]. Variables related to tobacco consumption also will be recorded: number of cigarettes smoked per day, start age, number of previous cessation attempts, longest period of cessation, and presence of other smokers in the family. The degree of nicotine dependence will be measured by the Fageström test. Motivation to stop smoking will be assessed by the Richmond test.

During follow-up visits, weight, height, and blood pressure will again be measured. Participants will be asked about their tobacco use and presence of withdrawal symptoms (vehement desire to smoke, anxiety, tension, nervousness, frustration, impatience, difficulty in concentrating, hunger, drowsiness or difficulty in sleeping, nightmares, headache, irritability/depression), and CO in exhaled breath will be measured by carboximetry.

At each visit, the professional who provided smoking cessation information (doctor or nurse) and any treatment provided will be recorded. We will also record the smoking cessation date (D-day) and the date of the end of follow-up, either 12 months after D-day or date lost to follow-up (D2). We will then calculate the length of the follow-up period. (With these variables the length of survival can be calculated: time interval between start date of smoking cessation and relapse or end of follow-up).

Tobacco abstinence will be confirmed by the level of carbon monoxide (CO), set as 10 parts per million or less, measured by carboximetry readings taken by trained personnel.

The follow-up period will have the following end-points: (1) 12 months after D-Day; (2) participant decides not to continue in the study, informs study personnel, and abandons participation; (2) participant is lost to follow-up, provides no more information, and will be considered relapsed as of that time point.

### Sample size/power calculation

To calculate sample size for each primary care centre, the number of individuals in a simple randomized design was multiplied by the design effect. Accepting an alpha risk of 0.05 and a beta risk of 20% in a bilateral contrast, 222 subjects are required in each group to detect a difference of at least 5% (calculations based on EPIDAT v. 3.1). To calculate design effect, we estimated the intracluster correlation coefficient (ICC) in clinical trials randomized by primary care clusters, generally less than 0.05 [12], and as a cluster size. The average size is 20 with a design effect of 1.36. Assuming these values, the definitive sample size for the study was set at 604 subjects, randomised as described above.

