## Background

Tobacco consumption is the most preventable cause of morbidity-mortality in the world. Although the prevalence of tobacco use among adolescents and young adults in Europe has decreased in recent years, tobacco use continues to be a major health problem among young people with a lower educational level. According to, data from ESCA 2011, 30.6% of boys and 34.1% of girls, among 15–24 years smoke daily.

Many adolescent and young adult smokers want to stop smoking and report frequent attempts to quit [1]. Valdivieso et al. [2] recently reported high interest in smoking cessation (67%) among young people who were habitual smokers and who frequently expressed the difficulty of maintaining abstinence despite repeated attempts.

Primary health care has an essential role in smoking cessation. Results of a randomized clinical trial in Spain indicate that a smoking cessation intervention was effective in the adult population, with 8.1% of the intervention group participants reporting continued abstinence at one year, compared to 5.8% in the control group (p<0.014) [3].

However, no studies to date assessed the effectiveness of a structured smoking cessation intervention directed at young people. One aspect of smoking cessation that merits in-depth study is the potential usefulness of new technologies, in particular the use of an application designed for smartphones (app), as a supportive element that could assist younger smokers in their efforts to quit. New technologies –and specifically a targeted app-- offer three benefits that can be useful for this purpose: First, they reach people “where they are”, i.e. there is no need to go to any specific place to receive support services. Second, they promote interactivity, opening new channels of communication between patients and “experts”. And third, they provide instant access to information and assistance. Therefore, it seems logical to hypothesize that a smartphone app will be a useful tool to offer additional support when a young adult wants to stop smoking [4].

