Some efforts have already been made in this direction. Clinical trials have evaluated the effectiveness of smoking cessation interventions in adolescents and young people that made use of text messages (SMS), with significantly better results than in the control group (9% vs. 4% abstinence) [5,6]. A recent review by Cochrane [7] of the effectiveness of smoking cessation interventions that use mobile telephones concludes that further studies are needed to determine whether these technologies will assist in smoking cessation efforts. Of particular interest for clinical practice, a programme of text messages sent to mobile phones was effective in the short term (six weeks) and a combined programme of Internet and mobile phone messages up to 12 months.

According to a study by Fundación Telefónica (the foundation associated with Spain’s national telephone company), the number of “smartphones” (mobile phones with an advanced operating system such as Android or iOS) sold in the second trimester of 2011 exceeded for the first time the number of personal computers sold (107 million smartphones, compared to 85 million personal computers). In 2009, more than two thirds of the world’s population had mobile phone access and more than 4.2 billion text messages were sent [4]. We would point out that the youngest segment of the population is most likely to include new technologies in their everyday lives. This behaviour pattern is repeated in patterns of Internet access using mobile phones and 3G technologies, reaching 26% market penetration among young people in Spain --more than twice the European average for this population [4].

Parallel to the growth of smartphone devices, a series of apps have been developed with the objective of providing information and support concerning social and medical problems [8]. The world market for medical apps for smartphones and tablets multiplied seven-fold in 2011 alone, reaching a total of US$718 million, according to a market analysis by the American firm *research2guidance*[9]. At present, these apps are being used as instruments of patient education and support and are also helpful to healthcare professionals [10].

Nonetheless, the market for health care apps is very fragmented; many are designed for very specific contexts or low-incidence diseases. To our knowledge, no randomized studies have assessed the effectiveness of smoking cessation attempts in young people motivated to stop smoking using a smartphone app.

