#### Randomisation

The unit of randomisation will be the primary care centre, stratified according to urban/rural location and number of participating professionals to ensure comparability between the study groups, and then assigned 1:1 to the intervention or control group. Randomisation will use the Epidat 3.0 programme.

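### The 222 per group stated for 80% power to detect a 5-point difference cannot be reproduced at either control abstinence rate the protocol cites; it needs a control rate of about 1.2%

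*Protocol article*

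**What the plan says.** The section on sample size and power sets the error rates ("Accepting an alpha risk of 0.05 and a beta risk of 20% in a bilateral contrast") and concludes that "222 subjects are required in each group to detect a difference of at least 5" per cent. It does not say which control or intervention abstinence rate was entered. It then inflates for clustering: the intracluster correlation (ICC) is described as "generally less than 0.05", and "The average size is 20 with a design effect of 1.36". The total is set at 604. Centres are "assigned 1:1 to the intervention or control group".

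The primary response, in the statistical analysis section, is continued abstinence at 12 months after the quit day.

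Control-group abstinence rates appear in only two places, both in the Background. An adult trial in Spain found "8.1% of the intervention group participants reporting continued abstinence at one year, compared to 5.8% in the control group". Text-message trials in adolescents and young people had "significantly better results than in the control group (9% vs. 4% abstinence"), which is itself a 5-point difference.

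**The concern.** For low proportions, the number needed to detect a fixed absolute difference rises quickly with the control rate. A figure of 222 for 5 points is small enough to imply that almost nobody in the control group stays abstinent. That does not fit the population or the comparator. Participants need a Richmond score of at least 5, and controls receive counselling under the Catalan Health Institute guideline.

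The figure of 222 is the base of the whole trial size. If it does not deliver 80% power for 5 points at plausible control rates, the article credits the design with a property it lacks. A null result could then be read as evidence against a 5-point benefit that the trial had roughly an even chance of missing.

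**Working it through.** **Inputs.** Two-sided alpha 0.05 (z = 1.960), power 80% (z = 0.842), 1:1 allocation, a 5-point difference read as absolute percentage points, design effect 1.36, average cluster size 20 and a total of 604, from the sample size and randomisation sections. Control rates of 4% and 5.8% come from the Background. The number of centres, 22, comes from the Discussion.

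**Step from 222 to 604.** 2 × 222 × 1.36 = 603.8, which rounds to 604. This step is consistent, so 222 is the figure to test.

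**Formula.** With p̄ = (p1 + p2)/2,

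n per group = [1.960·√(2p̄(1−p̄)) + 0.842·√(p1(1−p1) + p2(1−p2))]² / (p2 − p1)²

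**Reproducing 222.** Solving for the control rate with a 5-point difference gives about 1.19%. For 1.19% vs 6.19%: (0.5225 + 0.2224)² / 0.0025 = 222.0.

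**At the cited control rates.**
- 4% vs 9%: (0.6833 + 0.2919)² / 0.0025 = 380.4, so 381 per group.
- 5.8% vs 10.8%: (0.7647 + 0.3270)² / 0.0025 = 476.7, so 477 per group.

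With the design effect of 1.36 these become 519 and 649 per group, or 1,038 and 1,298 in total, against 604.

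**Does another formula rescue 222?** No. Control rate at which each version gives 222, and n per group at the cited rates:

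| Version | Control rate giving 222 | n at 4% | n at 5.8% |
|---|---|---|---|
| Pooled, two-sided | 1.19% | 381 | 477 |
| Unpooled, two-sided | 1.23% | 378 | 474 |
| Continuity-corrected, two-sided | 0.53% | 420 | 516 |
| Arcsine, two-sided | 1.6% | 368 | 468 |
| Pooled, one-sided | 2.2% | 300 | 376 |

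**Power for 5 points with 222 effective subjects per group.** z = [(p2 − p1)√n − 1.960·√(2p̄(1−p̄))] / √(p1(1−p1) + p2(1−p2)), and 0.05 × √222 = 0.7450.
- 4% vs 9%: (0.7450 − 0.6833)/0.3468 = 0.178, power 57%.
- 5.8% vs 10.8%: (0.7450 − 0.7647)/0.3886 = −0.051, power 48%.

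Exact binomial enumeration of the uncorrected test gives 57.4% and 48.1%.

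**Difference detectable with 80% power at 222 per group.**
- From 4%: 7.0 points (4% vs 11%: (0.7301 + 0.3107)² / 0.0049 = 221.07, rounded up to 222).
- From 5.8%: 7.9 points (5.8% vs 13.7%: (0.8222 + 0.3499)² / 0.006241 = 220.1, rounded up to 221).

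**Dependence on the clustering inputs.**
- A design effect of 1.36 at cluster size 20 implies ICC = 0.36/19 = 0.019.
- At ICC 0.05 and cluster size 20, the design effect is 1 + 19 × 0.05 = 1.95. The 302 per group are then worth 302/1.95 = 154.9, and power for 5 points is about 43% (from 4%) and 36% (from 5.8%).
- With 22 centres, 604/22 is about 27.5 per centre, not 20. At ICC 0.019 the design effect is 1 + 26.5 × 0.019 = 1.50, leaving about 201 effective per group. Power is then about 76% even for 4% vs 11%.

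**The case against.** **No control rate is stated.** The sample size section is therefore under-specified, and no input of its own contradicts it. The 4% and 5.8% come from the Background, describe other populations or interventions, and are never named as planning values. A condensed article may leave the assumed rate to the full protocol. This stands as a limit on the claim: the omission alone would not be a finding. But the article does state a result, and that result disagrees with every control rate it cites. An unseen document could supply a rate near 1.2%, but could not make 222 correct at 4% or 5.8%.

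**The planned analysis is a multi-level survival model.** Relapse timing may carry more information than the 12-month proportion. As an illustration that assumes proportional hazards and 444 effective subjects, a log-rank approximation gives about 84% power for 4% vs 9% and 70% for 5.8% vs 10.8%. This also stands as a limit. Proportional hazards is an assumption the document does not make. The stated calculation concerns a percentage difference, with no hazard ratio or event count, and the primary response is still 12-month abstinence.

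**Stronger readings that go too far.** A reader might infer that the trial's real power is 48% to 57%. The document does not support this, because the range rests on borrowed control rates, a two-proportion test and the 1.36 design effect. A reader might also infer that 4% vs 11% was what the authors entered, because it rounds up to 222. Other pairs do the same: 3% vs 10% with continuity correction also rounds up to 222.

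**Conclusion.** The concern holds in this form: the stated 222 per group does not give 80% power for 5 points at either control rate in the document, and the rate it requires, about 1.2%, has no support there. The shortfall is large: 381 or 477 per group would be needed before the design effect.

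The power figures of 57% and 48%, and the detectable differences of 7.0 and 7.9 points, are conditional on three things: a comparison of proportions at 12 months, a control rate of 4% to 5.8%, and a design effect of 1.36. They are not the known power of the trial. A higher ICC or larger clusters would lower them; an efficient survival analysis might raise power. That 222 cannot be reproduced at the cited rates does not depend on the design effect or the survival model. It should be corrected, because 222 is the only quantitative basis given for the trial's size.

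**What to change.** In the sample size section:

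1. State the control and intervention abstinence rates assumed, with their source.
2. Keep 604, and restate either the power for 5 points or the difference detectable with 80% power at those rates.
3. State the ICC used, and reconcile the cluster size of 20 with the 22 centres (about 27.5 participants each) before recomputing the design effect.

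A sentence such as 80% power for about 7 points (4% vs 11%) may be used only if it is stated to be conditional on the 1.36 design effect. It should not be presented as the origin of 222.

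The cost is one rewritten paragraph and a less favourable stated power or detectable difference. No extra patients are needed to correct the statement. Keeping 80% power for 5 points at the cited rates would be a different decision, with a total of about 1,038 to 1,298 at the stated design effect.

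### The ICC behind the design effect of 1.36 is not stated; it implies about 0.019, and the 80% power at 604 subjects holds only at or below that value and with 20 patients per centre

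*Protocol article*

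**What the plan says.** The section on sample size and power in the protocol article builds the total in two steps.

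- Individual randomisation: "Accepting an alpha risk of 0.05 and a beta risk of 20% in a bilateral contrast", it finds that "222 subjects are required in each group to detect a difference of at least 5" percent.
- Inflation for clustering: the ICC is described as, "in clinical trials randomized by primary care clusters, generally less than 0.05", with a literature reference. Then: "The average size is 20 with a design effect of 1.36". From these inputs, "the definitive sample size for the study was set at 604 subjects".

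No single ICC value is given as the planning assumption, and no control-group abstinence rate is given. The last paragraph of the Discussion states that 22 primary care centres take part. The Randomisation section allocates centres 1:1.

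**The concern.** The design effect carries the whole allowance for clustering: it takes 444 subjects to 604. The article presents the total as following from the inputs it prints, but those inputs do not yield 1.36. The only ICC figure on the page is 0.05, and a reader who uses it with 20 per centre gets a much larger design effect. The value that does give 1.36 appears nowhere, so nobody can judge whether it suits this outcome and setting.

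The cluster size is open to question too. The design effect uses 20 per centre, while 604 subjects spread over the 22 centres named in the Discussion is clearly more than 20.

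At stake is the meaning of the 80% power. It is stated without conditions, yet it depends on an undisclosed ICC and on a centre size that the trial's own numbers do not support.

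**Working it through.** **Inputs**

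- Two-sided alpha 0.05, power 80%, 222 per group (444 in all), average cluster size 20, design effect 1.36, total 604: sample size section.
- ICC: only the statement that it is generally below 0.05, same section.
- 22 centres: Discussion.

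**1. The plan's own figure**

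444 × 1.36 = 603.84, rounded up to 604 (302 per group). The total reproduces exactly from 222 and 1.36.

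**2. The ICC that 1.36 implies**

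Design effect DE = 1 + (m − 1) × ICC. With m = 20: ICC = (1.36 − 1)/19 = 0.0189, about 0.019. This is below 0.05, so it agrees with the text, but it is less than half of the figure cited.

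**3. The cluster size that 22 centres imply**

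604/22 = 27.5 per centre. Conversely, 22 × 20 = 440 subjects, and 604 subjects at 20 per centre would need 604/20 = 30.2 centres. (The total before inflation, 444/20 = 22.2, is close to 22 centres. The article does not say how 22 was reached.)

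**4. Power of 604 subjects**

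The effective size per group is n = 302/DE. If 222 per group gives 80%, then

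power = Φ[(1.960 + 0.842) × √(n/222) − 1.960].

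Example, m = 20 and ICC = 0.05: DE = 1 + 19 × 0.05 = 1.95; n = 302/1.95 = 154.9; √(154.9/222) = 0.835; 2.802 × 0.835 − 1.960 = 0.380; Φ(0.380) = 0.648.

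| ICC | DE, m = 20 | Power, m = 20 | DE, m = 27.5 | Power, m = 27.5 |
|---|---|---|---|---|
| 0.01 | 1.19 | 85% | 1.26 | 83% |
| 0.019 | 1.36 | 80% | 1.50 | 76% |
| 0.02 | 1.38 | 79% | 1.53 | 75% |
| 0.03 | 1.57 | 74% | 1.79 | 68% |
| 0.04 | 1.76 | 69% | 2.06 | 62% |
| 0.05 | 1.95 | 65% | 2.32 | 57% |

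(The columns for 27.5 use 604/22 unrounded.)

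**5. Subjects needed for 80% at 20 per centre**

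N = 444 × DE. At ICC 0.02 this is 444 × 1.38 = 612.7, so 613. At ICC 0.05 it is 444 × 1.95 = 865.8, so 866 (433 per group).

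**6. The largest ICC that 1.36 covers with 22 centres**

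0.36/(27.45 − 1) = 0.0136. With the centres as planned, the ICC would have to be at or below about 0.014 for the stated power to hold.

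**The case against.** A reader might infer that the plan assumes an ICC of 0.05, miscalculates the design effect as 1.36 where 1.95 is right, and is therefore under-sized. The article does not support that. It gives 0.05 as a level that ICCs usually stay below, not as the planning value. An ICC of about 0.019 fits that description, the step from 222 to 604 is exact, and nowhere does the article claim 80% power at ICC 0.05. Planning below a literature ceiling is legitimate, and nothing in the document shows that the true ICC exceeds 0.019. At ICC 0.02 the shortfall is only nine subjects (613 against 604). So there is no proven arithmetic error, and a loss of power is a possibility and not an established fact.

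It can also be said that the article is condensed. The ICC may stand in the full protocol or rest on the cited reference, and the sentence about cluster size is visibly incomplete, so a value may have dropped out.

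All of this limits the point without removing it. The article did not leave the calculation to another document: it printed an ICC range, a cluster size, a design effect and a total, and presented the last as the result of the others. The range it prints allows design effects up to about 1.95 at 20 per centre, so it does not support 1.36 in particular. And the mismatch between 20 per centre and 22 centres does not depend on any unseen source.

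**Conclusion.** The point holds in conditional form. The ICC used is not disclosed; it is about 0.019 by back-calculation. The stated 80% power at 604 subjects requires an ICC no higher than that and centres that average 20. At 20 per centre, power falls to about 74% at ICC 0.03 and about 65% at ICC 0.05.

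The cluster size is the firmer part. With 22 centres, 604 subjects average 27.5 per centre, so even the plan's implied ICC gives a design effect of about 1.50 and power of about 76%. At ICC 0.05 the figures are about 2.32 and 57%.

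These results rest on three assumptions: the usual design effect formula with equal centre sizes; a normal approximation for power; and 222 per group truly giving 80%. The last cannot be confirmed because no control rate is stated, and whether 222 is itself right is a separate question.

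**What to change.** Keep 604 and rewrite the sample size paragraph:

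- State the ICC used (about 0.019 if 1.36 is intended) and justify a value well below the 0.05 cited.
- Reconcile the average of 20 per centre with 22 centres and 604 subjects: either give the number of centres that 20 per centre requires (about 30), or use about 27.5 per centre and recompute the design effect.
- Replace the unconditional 80% with the design effect and the power of 604 subjects over ICC 0.01 to 0.05, at the reconciled cluster size, and state the control rate on which those powers rest.

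The cost is one rewritten paragraph and a short table. No change to recruitment or analysis is needed. The downside is that the stated power becomes less favourable over most of the ICC range that the article itself allows.

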### Intervention

During the recruitment period, or until the required quota of patients is reached, the family doctor and/or primary care nurse will invite patients aged 18 to 30 years who smoke 10 or more cigarettes per day to participate in the study. If the patient is eligible for inclusion and agrees to participate, informed consent will be requested (Figure 1). After signing informed consent, the participant’s demographic data will be collected and the study questionnaire will be administered (Fageström & Richmond). During this visit (visit 0) smokers with moderate motivation to stop smoking (Richmond score of 5–6) will be invited to schedule a second appointment to attempt to increase their motivation. For highly motivated participants (Richmond score of 7–10) a “quit day” will be established within the following 15 days (D-Day), and they will be invited to schedule an appointment for the day before their D-Day.

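### The design effect of 1.36 appears to assume centres of equal size; since sizes will vary and 604 has no reserve, power falls somewhat below 80% at the implied ICC (minor)

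*Protocol article*

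**What the plan says.** All of the calculation is in the protocol article, under Sample size/power calculation.

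- Error rates: "Accepting an alpha risk of 0.05 and a beta risk of 20% in a bilateral contrast".
- Size before clustering: "222 subjects are required in each group to detect a difference of at least 5" percent.
- ICC: no single value is printed. It is described only as "generally less than 0.05" in trials randomised by primary care cluster.
- Cluster size and inflation: "The average size is 20 with a design effect of 1.36".
- Result: "the definitive sample size for the study was set at 604 subjects".

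Under Randomisation, centres are "stratified according to urban/rural location and number of participating professionals" and "then assigned 1:1 to the intervention or control group". Under Intervention, inviting of patients continues "During the recruitment period, or until the required quota of patients is reached"; the quota has no number and no stated level (centre, arm or trial). The Discussion gives 22 participating centres.

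**The concern.** The factor 1 + (m − 1) × ICC is exact only when every cluster has m members. If sizes vary around a mean of m, the usual approximation is 1 + [(1 + CV²) × m − 1] × ICC, which is larger for any CV above zero. The section lists an ICC and a cluster size as its inputs and mentions no variation in size.

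The plan gives its own grounds to expect variation. It calls 20 an average, recruits centres on a voluntary basis, and stratifies them by number of participating professionals, which would serve little purpose if all centres had the same capacity.

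The planning claim of 80% power is at stake. Because the total is the bare product of the base size and the design effect, even a small understatement of the design effect takes power below 80%.

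**Working it through.** **Inputs from the article.** Two-sided alpha 0.05 and power 80%, so z = 1.960 + 0.842 = 2.802; 222 per group before clustering; average size 20; design effect (DE) 1.36; total 604, or 302 per arm at 1:1; 22 centres.

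**Assumption.** The CV of centre size is not given. A range of 0.3 to 0.6 is used.

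**Step 1: reproduce the plan's figure.** 2 × 222 × 1.36 = 603.84, rounded up to 604. The figure reproduces and leaves no reserve.

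**Step 2: implied ICC.** With equal sizes, 1 + 19 × ICC = 1.36 gives ICC = 0.36/19 = 0.0189.

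**Step 3: allow for unequal sizes.**
DE = 1 + [(1 + CV²) × m − 1] × ICC
Power = Φ(2.802 × √[(302/DE)/222] − 1.960)
Total for 80% power = 444 × DE, rounded up

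At m = 20 and ICC 0.0189:

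| CV | DE | Effective n per arm | Power | Total for 80% |
|---|---|---|---|---|
| 0 | 1.360 | 222.1 | 80.0% | 604 |
| 0.3 | 1.394 | 216.6 | 79.0% | 619 |
| 0.4 | 1.421 | 212.6 | 78.3% | 631 |
| 0.6 | 1.496 | 201.8 | 76.2% | 665 |

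For example, at CV 0.6: DE = 1 + (1.36 × 20 − 1) × 0.0189 = 1.496 and 302/1.496 = 201.8. Here 1.36 is 1 + 0.6², which only happens to equal the plan's design effect.

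**Step 4: efficient weighting.** The article plans a multi-level model, which can weight centres better than the formula above assumes. The relative efficiency against equal sizes is 1 − CV² × L(1 − L), with L = m × ICC/(m × ICC + 1 − ICC). At m = 20, L = 0.379/1.360 = 0.279 and L(1 − L) = 0.201.

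- CV 0.3: 1 − 0.09 × 0.201 = 0.982; DE = 1.36/0.982 = 1.385; power 79.3%.
- CV 0.4: 0.968; DE 1.405; power 78.7%.
- CV 0.6: 0.928; DE 1.466; power 77.0%.

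**Step 5: the mean size implied by the stated number of centres.** 604/22 = 27.5 per centre, whereas 22 × 20 = 440. At m = 27.5 and ICC 0.0189, with the formula of step 3:

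| CV | DE | Power |
|---|---|---|
| 0 | 1.501 | 76.0% |
| 0.3 | 1.548 | 74.7% |
| 0.4 | 1.584 | 73.8% |
| 0.6 | 1.689 | 71.0% |

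Moving the mean from 20 to 27.5 costs 4.0 points before any variation is allowed for. Variation then costs a further 1.3 to 5.0 points over the assumed range.

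**The case against.** **The equal-size formula is inferred.** The article prints neither a formula nor an ICC value, and the sentence that introduces cluster size is incomplete. A reader might infer that 1.36 can come only from the equal-size formula. That is too strong: 0.36/(1.16 × 20 − 1) = 0.0162 at CV 0.4 and 0.36/(1.36 × 20 − 1) = 0.0137 at CV 0.6 also yield 1.36, and both lie below the quoted bound of 0.05. This part of the objection stands. Equal size remains the natural reading, because the section names an ICC and a size as inputs and no CV.

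**Using the mean size is a common simplification.** The arithmetic as printed is right, and 20 is openly called an average. This also stands, and it is why the point is minor. It does not remove the point, because a total with no reserve cannot absorb the simplification.

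**Eager centres and unequal arms.** A reader might infer from the undefined quota that a few centres, or one arm, will supply most patients. The documents do not support that. The quota may well be per centre, the stratification works against imbalance between arms, and no figure for an uneven split of patients is given.

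**A per-centre ceiling as the remedy.** This might also suggest itself, but it does not follow from the plan's figures. A ceiling one third above 20 is 26.7, and 22 × 26.7 = 587, which is below 604. A ceiling also sets no minimum, so it would not by itself ensure a low CV.

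**Conclusion.** The point holds as a minor one. On the equal-size reading, with the implied ICC of 0.0189, any variation in centre size puts the power of 604 below the stated 80%. The direction does not depend on which CV is assumed; the size of the loss does. For an assumed CV of 0.3 to 0.6, power is about 79% to 76% at a mean of 20, or 79% to 77% with efficient mixed-model weighting. At the 27.5 per centre implied by 22 centres it is about 75% to 71%, against 76% with equal sizes.

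At a CV of 0.3 to 0.4 and a mean of 20, the loss is only 1 to 2 points. Two other features of the same calculation matter more. The implied ICC is well below the only printed figure: an ICC of 0.05 with 20 equal centre members gives DE = 1 + 19 × 0.05 = 1.95 and power of about 65%. The mean of 20 does not fit 604 over 22 centres. The allowance for unequal sizes belongs with the correction of those two inputs and does not replace it.

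**What to change.** In the sample size section:

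1. State the ICC used as a single value.
2. State a mean centre size consistent with 22 centres (604/22 = 27.5), or reconcile the number of centres with a mean of 20.
3. State an assumed CV of centre size.
4. Compute the design effect as 1 + [(1 + CV²) × m − 1] × ICC and restate the power that 604 gives.

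The cost is a few sentences and a less favourable power figure. No extra patients are needed if the sponsor accepts the restated power. Restoring 80% through numbers alone would take 619 to 665 subjects at a mean of 20, ICC 0.0189 and CV 0.3 to 0.6, and more at a mean of 27.5.
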